### Study approach

The study is expected to screen around 200–250 volunteers to recruit 150 volunteers required for this study. During the screening step, the volunteers will be subjected to a routine simple medical history and health screening to collect some data [age, gender, eating habits, occupation, lifestyle (smoking, alcohol, exercise), height, weight] as well as biochemical blood [full blood count (FBC), glucose, HBA1c, lipid profile, estimated glomerular filtration rate (EGFR), liver function tests (LFT)] and urine [full examination microscopy examination (FEME)] tests. Once the healthy volunteers are selected, they will be randomly assigned to one of the five study groups (
Table 1). The volunteers will be asked to attend three clinic sessions (days 0, 28 and 56) (
Figure 1). A trained phlebotomist will take blood via venepuncture, as shown in
Figure 1. After the blood-taking on day 0, the volunteers will be given a bottle containing sufficient test supplements for 28 days. The volunteers will be asked to take the supplement after dinner every day for 28 days.

**Figure 1. f1:**
[figure not shown]
Overview of the study approach.

The volunteers will be asked to return to the study site on day 28 for blood-taking (5 mL) and to receive an influenza vaccine. The volunteers will be given a second bottle containing sufficient supplements for another 28 days. The volunteers will return to the study site on day 56 for blood-taking (15 mL) (
Figure 1). Of the 15 mL of blood taken on Day 56, 10 mL will be sent to the Thomson Hospital medical diagnostic laboratory for various biochemical tests to establish the end-study parameters. At the second (day 28) and third (day 56) clinic visits, the volunteers will be asked to return the bottle with their supplement. The pill count will check compliance at each visit. In addition, the volunteers will be asked to maintain a normal balanced diet and exercise/activity regimen during the study period. They will be asked to keep a diary to record major deviations from their diet. The diary will be checked at each visit for any unusual entries.

### Intervention

The TRF used in this study will be Tocovid Suprabio
^TM^, manufactured by HOVID Ltd in Malaysia, and is a registered supplement in Malaysia that is sold as an over the counter (OTC) supplement in major pharmacies in Malaysia. The active ingredient of the Tocovid SupraBio
^TM^, called EVNol
^TM^ was manufactured by ExcelVite Sdn. Bhd., Malaysia. The TRF has received the generally regarded as safe (GRAS) status by the USA Food Development Authority (FDA).
^
35
^

The influenza vaccine used in this study will be the VaxigripTetra Influenza vaccine type A and B as per the WHO recommendations, which will be obtained from the Thomson Hospital’s pharmacy.

### Blinding

The supplements will be packed in identical bottles and packaging. Each package will be labelled anonymously with a running number. The supplements in the first four weeks will be labelled with a number and an additional label, “FIRST”, while supplements in the second four weeks will have the same number, but the additional label will be “SECOND”. All investigators and volunteers will be blinded to the intervention. Then, a simple randomisation process allocated the intervention package to the volunteers, where the first volunteer recruited will receive the first anonymous number with the label, “FIRST” while the second volunteer recruited will receive the second anonymous number with the label, “FIRST” and so on for their first four weeks of supplementation. When they return to the study site after four weeks, they will receive a supplement package having the same number as their first package but with the label, “SECOND”. Each subject will receive the package with the supplement having a number from the study nurse. The number on each bottle will correspond to a supplement listed in
Table 1, which only the principal investigator of the study will know. All other investigators in the study will be blinded to this information.

Unblinding will only occur at the end of the study after all data have been collected for analysis. However, if any of the subjects in the study were to experience any adverse effects, then unblinding will be permitted for the said volunteer for further action.

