**Methods:**

A single-centre, randomised, parallel, double-blinded, placebo-controlled clinical trial with balance allocation involving five arms will be conducted. The healthy volunteers recruited will be randomly assigned to one of the arms, and they will be asked to take the respective supplements (400 mg, 200 mg, 100 mg, 50 mg of TRF or placebo) daily with their dinner. The volunteers will receive the influenza vaccine after four weeks. They will be asked to return to the study site four weeks later. A blood sample will be taken for the study at baseline, four and eight weeks. Primary outcome measures will be antibody levels to influenza, blood leucocyte profile and cytokine production. Secondary outcomes will be correlating plasma vitamin E levels with immune responses, plasma proteins and gene expression patterns. The findings from this study will be published in relevant peer-reviewed journals and presented at relevant national and international scientific meetings.

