### Trial design

A single-centre, parallel, double-blinded, placebo-controlled with balanced randomisation into five arms (
Table 1).

**Table 1. T1:** Study groups.

Group	Daily supplementation (Day 0 to Day 56)	Number of volunteers	Influenza vaccine
A	Placebo (0 mg TRF)	30	Day 28
B	50 mg TRF	30	Day 28
C	100 mg TRF	30	Day 28
D	200 mg TRF	30	Day 28
E	400 mg TRF	30	Day 28
	Total volunteers	150	

TRF = Tocotrienol-rich fraction.

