### Sample size

The sample size was calculated using
G*Power version 3.1.9.4. With the power set at 80% and a 5% level of significance, the analysis showed that 26 subjects per arm were required to detect a large difference between groups. The effect size (d) was assumed to be 0.7, based on a previous study.
^
19
^ Assuming a 15% dropout rate in two months, 30 subjects per arm (150 subjects) will be enrolled.

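### The stated method, simple randomisation, does not deliver the balanced allocation of 30 per arm that the design, Table 1 and the sample size rely on

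*Protocol article*

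**What the plan says.** The protocol article presents the allocation as balanced in two places. The abstract's Methods paragraph describes a "placebo-controlled clinical trial with balance allocation involving five arms will be conducted", and the Trial design section says "placebo-controlled with balanced randomisation into five arms". Table 1 in that section gives 30 volunteers to each of groups A to E, 150 in total.

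The Sample size section depends on those numbers: "With the power set at 80% and a 5% level of significance, the analysis showed that 26 subjects per arm were required", followed by "Assuming a 15% dropout rate in two months, 30 subjects per arm (150 subjects) will be enrolled".

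The mechanism appears only under Blinding, where "a simple randomisation process allocated the intervention package to the volunteers". Packages carry running numbers and are issued in order of recruitment: "the first volunteer recruited will receive the first anonymous number with the label" FIRST, and so on. Each number is tied to one of the Table 1 groups. The article does not say how that list is produced, and it mentions no blocks, no other restriction and no fixed count of packages per group.

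**The concern.** Simple randomisation is a standard term: each participant is assigned independently, with no constraint on the totals. Read that way, it cannot promise the equal arms stated elsewhere in the article. This is more than a detail left to a fuller document, because the article names a method and that method conflicts with its own design statement and table.

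All four TRF doses are compared with one placebo arm, so a small placebo arm would weaken all four comparisons together. The sample size also has no slack to absorb an uneven split, since 30 less 15% is 25.5, already just under the required 26.

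**Working it through.** **Inputs.** From Sample size: power 80%, significance level 5%, d = 0.7, 26 required per arm, 15% dropout, 30 enrolled per arm. From Table 1: five arms, 150 in total. Sidedness is not stated.

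**The plan's own figure.** A one-sided two-sample t-test with d = 0.7 and 26 per arm has power 0.801, so the 26 is reproduced. (A two-sided test needs 34 per arm and has power 0.70 at 26; that is a separate matter.) The 30 follows from 26 × 1.15 = 29.9. Dividing instead, 26 / 0.85 = 30.6, gives 31.

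**Arm sizes under simple randomisation.** The five arm sizes follow a multinomial distribution with N = 150 and probability 0.2 for each arm.

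- Standard deviation of one arm size: √(150 × 0.2 × 0.8) = √24 = 4.90.
- Probability of exactly 30 in every arm: 150! / (30!)⁵ / 5¹⁵⁰ = 6.2 × 10⁻⁵, or 0.006%.
- Probability that one given arm has 25 or fewer: Binomial(150, 0.2) gives 0.180. As a check, (25.5 − 30) / 4.90 = −0.92, for which the normal tail area is also about 0.18.
- Probability that at least one of the five arms has 25 or fewer: 0.727 by exact convolution; 0.726 in 400,000 simulated allocations.
- From the same simulations, the smallest arm averages 23.8 (5th to 95th percentile 19 to 27) and the largest 36.5 (33 to 42).

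With a restricted list ending at 30 per arm, every arm starts at 30.

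**After dropout.** The 26 is the number needed after losses, so the comparison should also be made among completers. Each participant was assumed to drop out independently with probability 15%.

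| | Simple randomisation | Exactly 30 per arm |
|---|---|---|
| Some arm below 26 completers | 99.9% | 96.0% |
| A given arm below 26 completers | 50.9% | 47.5% |
| Mean power, one dose against placebo, one-sided | 0.782 | 0.792 |
| Mean power, one dose against placebo, two-sided | 0.675 | 0.686 |

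The mean power loss from simple randomisation is 0.792 − 0.782 = 0.010 one-sided and 0.686 − 0.675 = 0.011 two-sided.

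**The case against.** The strongest reply is that 'simple' is everyday wording. The bottles are numbered in advance, issued in sequence and linked to Table 1, which lists 30 per group. A list of 5 × 30 numbers shuffled once would fit everything in the article except that one word. This is plausible, and it means the arm-size figures are conditional on the technical reading. It does not remove the inconsistency: such a list is restricted allocation, so the Blinding section would still misname the method, and a reader cannot tell which procedure is used.

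Three further objections limit the point, and they stand.

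- A reader might infer that simple randomisation is what would usually push an arm below the planned 26. The documents do not support that. The 26 is a requirement after dropout, and with exactly 30 per arm some arm still falls short in 96% of cases. The 73% describes arm sizes at randomisation only.
- A reader might infer a serious loss of power. The average loss is about one percentage point.
- A reader might infer that arms unevenly spread over recruitment time would bias the antibody comparisons. Any valid random list, simple or shuffled, is free of systematic bias; chance imbalance over time adds variance. The article gives neither a recruitment duration nor an assay batching plan from which to size even that.

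**Conclusion.** The article contradicts itself on how participants are allocated. It states balanced arms of 30, and the one method it names does not produce them. If the words are taken technically, the stated split has a 0.006% chance of occurring, and arms of about 24 and 36 would be typical extremes. These figures assume independent assignment with equal probabilities and a total of exactly 150.

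The consequence is modest: roughly one percentage point of mean power per comparison, assuming d = 0.7 and independent 15% dropout, with an 18% chance that the shared placebo arm starts below 26. The documents do not establish that the arms will in fact be unequal, because a shuffled list of 30 per arm may lie behind the wording. The passages need to be reconciled because the allocation method is a basic feature of the trial and the present text leaves it ambiguous.

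**What to change.** In the Blinding section, replace the reference to simple randomisation with a restricted method that delivers the stated design. One suitable wording: the package list is generated by computer in permuted blocks of randomly varying size, in the ratio 1:1:1:1:1, ending at exactly 30 packages per arm. Block sizes must be multiples of five. If a shuffled list of 30 packages per arm already exists, keep it and correct the wording to say so.

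The cost is one sentence, plus a new list if the current one was drawn without restriction. As a protocol change it also needs the ethics committee approval that the article requires. The Study status section reports that volunteers are still being screened, so the change should be possible before packages are issued. However, the Blinding section puts the allocation in the past tense, so the sponsor should first check whether a list has been drawn and how. Stratification is not needed to resolve this point.

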## Protocol

### Ethics consideration

The Monash University Human Ethics Committee (MUHREC) have reviewed and approved the study protocol [MUHREC 30401] (27 January 2022). In addition, the study will be conducted in accordance with the principles of the Declaration of Helsinki 2013 and the Malaysian laws on medical research involving human subjects. All changes to changes to the protocol will require approval from MUHREC before they are applied. All data, including personal information about potential and enrolled participants for this study, will be stored in a file kept in a locked cabinet in a locked room in Monash facilities. The digital data will be stored on a secure shared drive behind the Monash firewall. Only the chief investigator will have access to these files. Upon completion of the study, all data will be stored and handled by Monash University Malaysia for at least 15 years after the study has ended. Only researchers listed in the ethics approval will have access to the research data.

This protocol has been registered with the Australian New Zealand Clinical Trials Registry (ANZCTR) [
ACTRN12622000844741] on 15 June 2022.

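### The Blinding section says every investigator is blinded yet gives the bottle code to the principal investigator, so allocation is not concealed from that role and nothing keeps the role out of selection, assays or analysis

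*Protocol article*

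**What the plan says.** The Trial design section describes the study as "A single-centre, parallel, double-blinded, placebo-controlled with balanced randomisation into five arms", with 30 volunteers in each arm (Table 1). Who is blinded, and who is not, is set out in the Blinding section.

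- General statement: "All investigators and volunteers will be blinded to the intervention".
- Custody of the code: each bottle number stands for one of the Table 1 supplements, "which only the principal investigator of the study will know".
- The sentence after that: "All other investigators in the study will be blinded to this information".
- Issue of packages: they carry running numbers, and "the first volunteer recruited will receive the first anonymous number", the second volunteer the second number, and so on. The study nurse hands them over.
- Timing: the code is to be broken only once all data are in, with an exception for an individual volunteer who has an adverse effect.

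The Study plan section describes selection. From 200 to 250 people screened, 150 eligible volunteers are taken who have the lowest anti-influenza antibody and low plasma vitamin E. It gives no threshold for vitamin E and does not say how the two criteria combine.

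**The concern.** A double-blind trial relies on two separate protections. Before allocation, nobody who can influence who enters, or in what order, should know the next assignment. After allocation, nobody who can influence measurement or analysis should know the arms. As written, the first protection fails for the principal investigator, and the second is not secured for that role.

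The first matters more here. If the list is known and packages follow recruitment order, control over the order of entry amounts to control over who receives which arm. The selection criteria leave room for judgement, and both selection measures, antibody level and plasma vitamin E, also appear among the primary outcomes in the Outcomes section. An imbalance introduced at entry would bear directly on the comparison of interest, and no later analysis could be relied on to remove it.

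**Working it through.** No arithmetic decides this point. The check sets the statements side by side.

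**Step 1: is the principal investigator blinded?** The general statement covers all investigators. The custody sentence makes the principal investigator the one person who knows what each number contains. The next sentence limits blinding to the *other* investigators, which confirms that the principal investigator is the exception. The general statement is therefore untrue for one role.

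**Step 2: when is the code known?** The section puts unblinding after data collection, apart from individual adverse effects. The custody sentence sets no date and describes knowledge held while packages are being issued. One investigator thus knows the code before the stated time, which is a second conflict within the section.

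**Step 3: does knowing the code reveal future allocations?** Package numbers run in sequence and are issued in sequence ("where the first volunteer recruited will receive the first anonymous number with the label"). After *k* volunteers have entered, the next package is number *k* + 1. Anyone who knows what number *k* + 1 contains knows the next volunteer's arm before that person enters. This holds for every number in the list: 5 arms × 30 = 150 allocations.

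**Step 4: is there room for that knowledge to act at entry?** The Study plan ranks on antibody but asks only for low vitamin E, with no cut-off and no combining rule. Two people applying it to the same screened volunteers could choose different sets. No section fixes the order in which selected volunteers are entered.

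**Step 5: is there room for it to act later?** The text leaves some choices open. The antibody assay may use either of two conjugates, with a stop time anywhere from 10 to 20 minutes (Laboratory tests). Comparisons are with baseline and/or placebo, by one of two tests depending on the distribution (Statistical analysis). The article does not say who makes these choices.

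**Step 6: is the principal investigator kept away from these steps?** The article names a physician for consent, a phlebotomist for blood-taking, the study nurse for handing out packages and the hospital laboratory for biochemistry. It assigns nobody to the selection decision, the order of entry, the immune assays or the analysis, and no sentence excludes the principal investigator from any of them.

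Steps 1 to 3 follow from the text alone. Steps 4 to 6 show that the exposure is not closed off; they do not show that it is used.

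**The case against.** The strongest reply is that the article discloses the exception. The sentence about the other investigators can be read as qualifying the general statement. Volunteers and all other investigators remain blinded, the bottles and packs look alike, and the nurse is not said to hold the code. This much stands: a reader might infer that the trial is not double-blind in any useful sense, and the documents do not support that. They support a narrower statement, that one investigator is unblinded contrary to the section's own general claim.

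Second, the article gives the principal investigator no part in enrolment, assays or analysis, and a journal article may leave delegation of roles to the full protocol. It would be wrong to state as fact that the person steering selection or choosing tests knows the arms. But the article does more than omit a detail: it states who holds the code, and does so in conflict with its own claim of blinding.

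Third, the Study approach section places selection before random assignment. If all 150 were chosen before the first package was issued, the code could affect only the order of entry. That narrows the route without closing it, because order determines the arm.

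Fourth, the outcomes are laboratory measures, which leave less room for biased assessment than subjective ratings. This is fair, but it does not protect against selection at entry.

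Three further inferences should be resisted:

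- The Ethics consideration section says of the participant files that "Only the chief investigator will have access to these files". A reader might conclude that one person controls both code and data. The article does not say that chief and principal investigator are the same role, and the same paragraph opens the research data to the researchers listed in the ethics approval.
- The adverse-effect exception might suggest frequent unblinding. It permits a code break for the individual concerned, for further action; it does not require one, and the article gives no adverse-effect rate from which to estimate a number.
- Plasma vitamin E results might reveal dose to those running the immune assays. Nothing in the article says that those staff see the results.

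**Conclusion.** The point holds in its limited form. The Blinding section contradicts itself on whether the principal investigator is blinded and on when the code is first known. Because packages are issued in sequence, all 150 allocations are open in advance to that one role, and nothing in the article separates it from selection, order of entry, assays or analysis.

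The size of any bias cannot be given. It depends on what the principal investigator does in practice, which the article does not state; if that role has no hand in those steps, the effect could be nil. The conclusion rests on reading the custody sentence at its face value, as knowledge held during recruitment, and on packages being issued strictly in numerical order as described. It does not rest on any assumption about misconduct, data access or the frequency of adverse effects.

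**What to change.** **Preferred.** Have the list linking numbers to supplements generated and held by someone independent of recruitment, assessment and analysis, for example the hospital pharmacy or the packaging supplier. Keep the principal investigator blinded until the data are locked. Replace the custody sentence accordingly, so that the general statement about investigators becomes true.

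**Fallback.** If the principal investigator must keep the code, say plainly that this role is unblinded. Exclude it in writing from selection, enrolment (including the order of entry), assays and analysis, and correct the sentence that says all investigators are blinded.

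**Cost.** A change of custody and a short amendment, which under the Ethics consideration section needs ethics committee approval before it is applied. The Study status section puts the trial at screening, so the change can still be made before volunteers are allocated. Neither option alters the supplements, the visits or the handling of adverse effects.

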### Criteria for discontinuation

TRF has received the GRAS status from the US FDA.
^
35
^ Hence, severe adverse effects following the consumption of TRF are not expected. However, volunteers can drop out of the study at any time if they experience any side effects or do not want to continue with the study.

